## Abstract

**Background:**

Head and neck cancer (HNC) is the sixth most common cancer worldwide, and the functional, psychological and social consequences of HNC cancer and its treatment can be severe and chronic. Dysphagia (swallowing problems) affects up to two thirds of patients undergoing combined chemoradiotherapy. Recent reviews suggest that prophylactic swallowing exercises may improve a range of short- and long-term outcomes; however, the importance of psychological and behavioural factors on adherence to swallowing exercises has not been adequately studied. This study aims to develop and test the feasibility of a Swallowing intervention Package (SiP) designed in partnership with patients, speech and language therapists (SLTs) and other members of the head and neck multi-disciplinary team (MDT), for patients undergoing chemoradiotherapy (CRT) or radiotherapy (RT) for head and neck cancer.

**Methods/design:**

This feasibility study uses quantitative and qualitative research methods, within a quasi-experimental design, to assess whether patients will tolerate and adhere to the SiP intervention, which aspects of the intervention can be implemented and which cannot, whether treatment fidelity can be achieved across different contexts, whether study processes and outcome measures will be feasible and acceptable and to what extent the intervention is likely to have an impact on swallowing dysfunction and quality of life. Patients are being recruited from five sites in Scotland and England (three interventions and two usual care). The SLT based in the relevant intervention centre teaches the exercise programme and provides supporting materials. A combination of patient-reported outcome measures (PROMs), adherence measures and clinical swallowing assessments are used prior to intervention (baseline), at the end of treatment, 3 and 6 months post-treatment.

**Discussion:**

This collaborative study has taken a unique approach to the development of a patient-centred and evidence-based swallowing intervention. The introduction of an e-SiP app provides an exploration of the use of technology in delivering this intervention. The study provides an opportunity to examine the feasibility of delivering and participating in a supported swallowing intervention across several different NHS sites and will provide the evidence needed to refine intervention and study processes for a future trial.

**Trial registration:**

NCRI portfolio, 18192 & 20259

## Background

Head and neck cancer (HNC) is the sixth most common cancer worldwide [1]. Currently, there are more than 62,000 people living with head and neck cancer in the UK [2]. In Scotland, where incidence rates are significantly higher than the rest of the UK, a 37 % rise is predicted in the next 10 years [3]. Patients are surviving longer and, due to human papillomavirus, are younger at diagnosis. The functional, psychological and social consequences of HNC cancer and its treatment can be severe and chronic. Treatment includes a combination of surgery, radiotherapy and/or chemotherapy, and the side effects of these can interfere with some of the most fundamental aspects of daily living, including eating, drinking, communication and appearance. Improved survival has been achieved at the expense of increased morbidity, especially in relation to swallowing problems or ‘dysphagia’ [4].

Dysphagia affects up to two thirds of patients undergoing combined chemoradiotherapy (CRT) [5]. Patients report major deterioration in their swallowing, and little evidence of recovery over time, with younger survivors reporting the most severe problems [6]. Early side effects of CRT^1^ include pain, mucositis (inflammation of the mucous membranes) and xerostomia (dry mouth). Late effects include fibrosis (scarring) of the soft tissues, affecting the safety and efficiency of swallowing [7, 8]. Aspiration rates (food or fluid entering the airway) are high (≥60 %), leading to frequent hospitalisation for chest infection, pneumonia and even death [5, 8]. The effects of CRT contribute to significant weight loss, and 50–70 % of patients require a feeding tube during or after treatment [9]. Tube dependency reduces the need to swallow, so increasing the likelihood of fibrosis of the muscles involved in swallowing, and in the long-term, ‘disuse atrophy’, sometimes leading to complete inability to swallow. Swallowing difficulties have a significant negative emotional and physical impact on social eating, return to work and everyday quality of life [7].

Recent reviews [10, 11] suggest that prophylactic swallowing exercises may improve a range of short- and long-term outcomes, as they increase the blood flow to muscles, reducing or preventing fibrosis, and maintaining the range and speed of swallowing movements. However, not all trials have had positive results [12–14], and a number of questions remain, including the optimal timing, selection and duration of exercises, the achievement of intervention fidelity and, importantly, the support necessary to improve adherence [10]. Only 13–14 % of participants practise swallowing exercises as recommended [15, 16]. An unpublished study found that patients with high levels of pain during treatment struggled with performing regular exercises and that it was difficult to focus on preventative exercises in the context of facing a potentially life-limiting disease. Furthermore, the intervention was not seen as integral to their overall care [17]. There is, however, evidence that those who maintain their exercise schedule achieve improved swallowing outcomes [18] and are significantly less likely to need a feeding tube [19]—an important consideration given that feeding tubes are associated with significantly poorer quality of life [20].

The multi-dimensional nature and impact of swallowing difficulties and the importance of psychological and behavioural factors on adherence to swallowing exercises has not been adequately studied [21, 22]. The need for further research, particularly prospective randomised trials to investigate the benefit of an intervention which includes pre-, peri- and post-treatment swallowing exercises has been highlighted repeatedly [10, 23, 24].

This study aims to develop and test the feasibility of a Swallowing intervention Package (SiP) designed in partnership with patients, speech and language therapists (SLTs) and other members of the head and neck multi-disciplinary team (MDT), for patients undergoing primary or adjuvant CRT or radiotherapy for head and neck cancer. A development phase (phase 1), informed by focus groups with patients and consensus workshops with professionals, produced a swallowing exercise schedule, staff manual and SiP package for patients, including written materials, videos, reminder materials and an electronic e-SiP ‘app’ to support adherence. This protocol, based on version 5 (24.2.16) describes the feasibility study (phase 2) for this complex intervention, which aims to answer four research questions in preparation for a future multi-centre trial:What is the feasibility of delivery and potential impact of the SiP for patients and head and neck cancer teams?What are the barriers and facilitators to adherence and fidelity to the SiP?Does an e-support system (e-SiP) have potential to support patients to perform their exercises and for collecting patient-reported data through video diaries?Are the study processes and outcome measures feasible and acceptable to patients and staff?

## Methods/design

This feasibility study uses quantitative and qualitative research methods, within a quasi-experimental parallel group design, to assess whether patients will tolerate and adhere to the SiP intervention, which aspects of the intervention can be implemented and which cannot, whether treatment fidelity can be achieved across different contexts, whether study processes and outcome measures will be feasible and acceptable and to what extent the intervention is likely to have an impact on swallowing dysfunction and quality of life.

Forty patients will be recruited to the SiP intervention group, from three hospital outpatient settings in Scotland, and a maximum of 30 patients will be recruited to a ‘usual care’ group, from sites in Scotland and the North East of England. This is a pragmatic design to allow for different service delivery models in different geographical areas. There is a trade-off between precision (recruitment parameter of numbers retained by study endpoint) and number of patients recruited to the study. A sample size of 59 is thought to be sufficient to identify any potential problems in feasibility which have a 5 % probability of occurrence at least once, with 95 % confidence [25]. Several new sites have expressed an interest in participating and are being adopted in order to enhance recruitment.

To identify the variety of practical issues and problems faced by a ‘real world’ and inclusive ‘typical’ cohort of patients with head and neck cancer and the applicability of the intervention across this cohort, we will include people with/without prophylactic feeding tubes, from different demographic, diagnostic (e.g. oral, pharyngeal, laryngeal) and treatment (CRT and radiotherapy alone) groups.

Inclusion criteria:

Patients diagnosed with an index primary mucosal squamous cell carcinoma of oral cavity, nasopharynx, pharynx or larynx or unknown primary, who are planned for chemoradiotherapy or radiotherapy ≥30 fractions. This may include patients who have undergone surgery before their chemoradiation or radiotherapy. Patients must be able to give informed consent.

Exclusion criteria:

Patients with synchronous or metachronous head and neck cancer primaries, those undergoing palliative treatment, non­English speakers, previously diagnosed dysphagia unrelated to HNC and those who have undergone total glossectomy or total laryngectomy.

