### Screening, recruitment and consent

All potentially eligible patients will be identified from the head and neck cancer MDT meetings. Eligible patients will be seen at routine appointments for treatment planning and invited to participate in the study by a member of the clinical team. The e-SiP app is being tested in Tayside, where patients eligible for the intervention are also eligible for the app version. The delegated individual will explain the study to the patient, give them the Patient Information Sheet (PIS) and answer any questions. Consent will be sought a minimum of 24 h later by a research nurse. The PIS for the intervention group explains that a Swallowing intervention Package of exercises and support has been developed and that we are now asking people to try this out and report their experiences, with the hope that we will be able to use these findings to underpin a larger trial. The PIS for the control group explains that patients will have no change to their usual care and will continue to have the swallowing support normally provided by their treatment centre. Both intervention and control patients are informed that taking part in the study will not affect any usual treatment that they may receive and that taking part may not benefit them personally.

At the time of consent the participant will also be asked to fill in the baseline study questionnaires, and a standard letter will be sent to their GP specifying the recruiting hospital and whether or not the patient is in the intervention or ‘usual care’ group. All patients will also be asked whether they and/or a close family member or friend would be willing to be approached for a subsequent qualitative interview with the research fellow, between 6 weeks and 3 months after treatment finishes, to explore their experiences.

In order to assess the representativeness of the sample, a screening log will record the number of patients who are (a) ineligible, (b) refuse to participate in the intervention or control cohorts and (c) decline specific aspects of the study (e.g. clinical assessments, questionnaires), as well as their reasons, where possible. The rights of patients to refuse to participate or withdraw without giving reasons will be respected. If patients do volunteer a reason for refusal, or for wishing not to use the e-SiP app versions, then these will be logged.

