Statistical models utilising the repeated measures, with baseline measures used as covariates in statistical models will be used to ascertain likely key independent predictors explaining variability of the range of possible outcome measures in this feasibility study. We do not expect to achieve significant differences from baseline to follow-up measure(s) between or within groups as this study is inadequately powered and is quasi-experimental; however, we expect to estimate relative effect sizes (and 95 % CI) for each potential main outcome measure, correlation between measurements, and intra-cluster (site) correlation coefficient for use in sample size simulations for a future randomised trial; this study aims to ascertain if the data collection is sufficient to yield usable data in hypothesis testing in a definitive multi-centre trial and to assess whether the direction of effect is in favour of the intervention. Preliminary psychometric validation of the RIB will also be undertaken, including Cronbach’s alpha (for internal consistency), correlation analyses for test-retest reliability and construct validity. The EQ-5D will be used to calculate quality-adjusted life years (QALY) gains and used along with an assessment of resource implications to inform a full economic evaluation in a future definitive trial. With respect to the analysis of the e-SiP, the e-SiP itself is not considered part of the intervention (it does not represent any change in actual exercise protocol), but is a means of testing different ways of data collection, improving any missing data problem and supporting adherence. Although we intend to incorporate the e-SiP data into our analysis, our sample of patients using the e-SiP will be very small due to the available number of iPads. However, we will conduct a sensitivity analysis whereby we analyse the data with and without the e-SiP sub-sample to ascertain if there are any changes to effect size and variance. We will assess e-SiP use to see which aspects of the app patients use most and to conduct a comparison of entries between the paper and e-SiP diaries.

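### The 59-patient detection claim covers any feasibility problem, but for problems specific to SiP only 40 patients count, giving 87 % confidence at a 5 % rate instead of 95 %

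*Protocol article*

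**What the plan says.** Methods/design sets the group sizes first. For the intervention it says: "Forty patients will be recruited to the SiP intervention group, from three hospital outpatient settings in Scotland". The limit for the comparison group reads: "a maximum of 30 patients will be recruited to a ‘usual care’ group". The total is therefore at most 70. The same paragraph then justifies the size: "A sample size of 59 is thought to be sufficient to identify any potential problems in feasibility". It specifies the problems meant as those "which have a 5 % probability of occurrence at least once, with 95 % confidence". No separate figure is given for the SiP group. New sites are being adopted to help recruitment, but no SiP target above 40 is stated.

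The opening of Methods/design lists the aims, which begin: "to assess whether patients will tolerate and adhere to the SiP intervention, which aspects of the intervention can be implemented and which cannot". Fidelity across settings follows. The first two research questions at the end of the Background likewise concern delivery and potential impact of SiP, and adherence and fidelity to it. The fourth concerns study processes and outcome measures. On the comparison group, the section on screening, recruitment and consent says: "The PIS for the control group explains that patients will have no change to their usual care".

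**The concern.** A statement of this kind holds only if every patient counted could show the problem in question. Neither group reaches 59 on its own, so the claim must rest on both groups together. For consent, questionnaires, clinical assessments and retention that is sound, because all patients go through these steps. For tolerance of, adherence to, delivery of and fidelity to SiP it is not, because usual-care patients do not receive SiP and cannot reveal such a problem. The sentence makes no such distinction.

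At stake is how a clean result would be read. If a given SiP-specific problem is never seen among the 40 patients, a reader relying on this sentence could take a 5 % problem to be ruled out with 95 % confidence. The design gives less assurance than that for the first two research questions.

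**Working it through.** **Inputs, all from the protocol article**

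- Problem probability per patient: p = 0.05 (Methods/design).
- Required confidence of at least one occurrence: 0.95 (Methods/design).
- Stated sample size: 59 (Methods/design).
- SiP group: 40. Usual care: at most 30. Total: at most 70 (Methods/design).
- Usual-care patients are not exposed to SiP (Screening, recruitment and consent).

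**Formula.** For n independent patients who could each show the problem, P(at least one) = 1 − (1 − p)^n.

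**Step 1: reproduce the stated figure.** Solving 1 − 0.95^n ≥ 0.95 gives n ≥ ln(0.05)/ln(0.95) = 58.40, hence 59. Check: n = 58 gives 94.9 % and n = 59 gives 95.2 %. The stated figure reproduces.

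**Step 2: processes shared by both groups.** At the maximum total, 1 − 0.95^70 = 0.9724, or 97.2 %. The claim is met, with 70 − 59 = 11 patients to spare.

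**Step 3: problems specific to SiP.** With n = 40, 1 − 0.95^40 = 0.8715, or 87.1 %. The chance of missing a 5 % problem altogether is 12.9 %, against the 5 % implied by the statement.

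**Step 4: the rate that 40 patients do cover at 95 % confidence.** Solving 1 − (1 − p)^40 = 0.95 gives p = 1 − 0.05^(1/40) = 0.0722, or about 7.2 %.

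| Problem type | Patients who can show it | Chance of seeing a 5 % problem | Smallest rate covered at 95 % |
|---|---|---|---|
| As stated | 59 | 95.2 % | 5.0 % |
| Shared processes | up to 70 | 97.2 % at 70 | 4.2 % at 70 |
| Specific to SiP | 40 | 87.1 % | 7.2 % |

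**The case against.** The strongest defence is that the sentence refers to the study as a whole. It speaks of a sample size directly after both groups have been described, and never assigns 59 to the SiP group. The arithmetic is right, the total exceeds 59, and the spare 11 of 70 (about 16 %) leave room for losses. The wording is also hedged. All of this stands for shared processes. It does not rescue the claim for SiP-specific problems, because the sentence covers all feasibility problems and the leading aims are about SiP.

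A second defence is that little depends on the figure. The article plans descriptive summaries with precision, no significance tests, and no rule that turns the absence of a problem into a decision. SiP-specific problems are also sought through weekly logs, observed consultations, diaries and interviews. The known adherence problem is far commoner than 5 %: the Background reports that only 13–14 % of participants exercise as recommended. At a 10 % rate, 40 patients would show a problem at least once with probability 1 − 0.9^40 = 98.5 %. This also stands, and it limits the severity.

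A reader might infer more than the article supports:

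- **That drop-out lowers the figure well below 87 %.** No attrition rate is given. Withdrawal and non-adherence are themselves problems to be observed, and a patient lost late has already been through the teaching and on-treatment phases.
- **That clustering by site lowers it further.** It could, but the size would rest on an assumed intra-cluster correlation, which the Data analysis section lists as something the study will estimate.
- **That the app is wrongly included.** The Data analysis section does not count the app as part of the intervention and already concedes that "our sample of patients using the e-SiP will be very small due to the available number of iPads".

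**Conclusion.** The statement is too broad as written. It is correct for study processes common to both groups and incorrect for problems that only SiP patients can have. For those, the confidence at a 5 % rate is 87.1 %, 7.9 points below the stated 95 %. Equivalently, 95 % confidence applies from a rate of about 7.2 % instead of 5 %.

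This rests on the article's own 40, 5 % and 95 %, and on the conditions the formula needs: all 40 patients are recruited and observed, and they behave independently. No outside figure is needed.

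A reader might go further and conclude that 59 is miscalculated or that the study is too small. The documents support neither. The fault lies in the scope of one sentence, and the severity is minor to moderate.

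**What to change.** Keep the recruitment numbers and reword the justification in Methods/design. Possible text: *Across both groups, 59 patients are enough to see at least once, with 95 % confidence, a problem in shared study processes that has a probability of 5 %. For problems specific to SiP, the 40 intervention patients give 87 % confidence of seeing at least once a problem with a probability of 5 %, and 95 % confidence for a probability of about 7 % or more, assuming that all 40 are observed and independent.*

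The cost is wording only. Recruitment, data collection and analysis do not change, and the one downside is a slightly less favourable stated figure. Keeping 5 % and 95 % for SiP-specific problems would instead need 59 SiP patients, which is 59 − 40 = 19 more than planned. Nothing in the article makes that necessary.

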### Screening, recruitment and consent

All potentially eligible patients will be identified from the head and neck cancer MDT meetings. Eligible patients will be seen at routine appointments for treatment planning and invited to participate in the study by a member of the clinical team. The e-SiP app is being tested in Tayside, where patients eligible for the intervention are also eligible for the app version. The delegated individual will explain the study to the patient, give them the Patient Information Sheet (PIS) and answer any questions. Consent will be sought a minimum of 24 h later by a research nurse. The PIS for the intervention group explains that a Swallowing intervention Package of exercises and support has been developed and that we are now asking people to try this out and report their experiences, with the hope that we will be able to use these findings to underpin a larger trial. The PIS for the control group explains that patients will have no change to their usual care and will continue to have the swallowing support normally provided by their treatment centre. Both intervention and control patients are informed that taking part in the study will not affect any usual treatment that they may receive and that taking part may not benefit them personally.

At the time of consent the participant will also be asked to fill in the baseline study questionnaires, and a standard letter will be sent to their GP specifying the recruiting hospital and whether or not the patient is in the intervention or ‘usual care’ group. All patients will also be asked whether they and/or a close family member or friend would be willing to be approached for a subsequent qualitative interview with the research fellow, between 6 weeks and 3 months after treatment finishes, to explore their experiences.

In order to assess the representativeness of the sample, a screening log will record the number of patients who are (a) ineligible, (b) refuse to participate in the intervention or control cohorts and (c) decline specific aspects of the study (e.g. clinical assessments, questionnaires), as well as their reasons, where possible. The rights of patients to refuse to participate or withdraw without giving reasons will be respected. If patients do volunteer a reason for refusal, or for wishing not to use the e-SiP app versions, then these will be logged.

